
|                            |                                                                                                                                                                                                                                                                                                                                                                                                                                                                                                                                                                                                                                                                                                                                                                                                                                                                                                                                                                                                                                                                                                                                                                                                                                                                                                                                                                        |
|----------------------------|------------------------------------------------------------------------------------------------------------------------------------------------------------------------------------------------------------------------------------------------------------------------------------------------------------------------------------------------------------------------------------------------------------------------------------------------------------------------------------------------------------------------------------------------------------------------------------------------------------------------------------------------------------------------------------------------------------------------------------------------------------------------------------------------------------------------------------------------------------------------------------------------------------------------------------------------------------------------------------------------------------------------------------------------------------------------------------------------------------------------------------------------------------------------------------------------------------------------------------------------------------------------------------------------------------------------------------------------------------------------|
|                            | 22. Unable to complete the follow-up (e.g. dementia, alcoholism, substance abuse, severe mental disease).                                                                                                                                                                                                                                                                                                                                                                                                                                                                                                                                                                                                                                                                                                                                                                                                                                                                                                                                                                                                                                                                                                                                                                                                                                                              |
| Therapeutic regimen | 
Patients who meet the requirements are randomly assigned to one of the following four groups according to the ratio of 1:1:1:1:
 
A: Intensive antiplatelet therapy + immediate intensive statin therapy (atorvastatin 80mg/d)
 
B: Intensive antiplatelet therapy + delayed intensive statin therapy (atorvastatin 40mg/d)
 
C: Standard antiplatelet therapy + immediate intensive statin therapy (atorvastatin 80mg/d)
 
D: Standard antiplatelet therapy + delayed intensive statin therapy (atorvastatin 40mg/d)
 
Intensive antiplatelet therapy :
 
Day 1: Clopidogrel 300mg/day+aspirin100-300mg/ day
 
Day2 - Day21±2: Clopidogrel 75mg/day+ aspirin 100mg/day
 
Day22±2 -Day 90: Clopidogrel 75mg/day+ aspirin placebo
 
Standard antiplatelet therapy :
 
Day 1: Aspirin 100-300mg/day + clopidogrel placebo
 
Day 2 - 90: Aspirin 100mg/day+ clopidogrel placebo
 
Immediate intensive statin therapy (atorvastatin 80mg/d):
 
Day 1 -Day 21±2: Atorvastatin 80mg/day
 
Day22±2 -Day 90: Atorvastatin 40mg/day
 
Delayed intensive statin therapy (atorvastatin 40mg/d):
 
Day 1 - Day3: Atorvastatin placebo
 
Day4 - Day21±2: Atorvastatin 40mg/day + Atorvastatin calcium placebo
 
Day22±2 -Day 90: Atorvastatin 40mg/day
 |
| Study Outcomes      | 
Primary outcome:
 
Stroke (ischemic or hemorrhagic)
 
Secondary outcomes:
 
 
• Composite vascular events: stroke (ischemic or hemorrhagic), myocardial infarction, or cardiovascular death.
 
• Ischemic stroke
 
• TIA
 
• Severity of stroke or TIA on an ordinal scale (a six-level ordered category scale combined vascular events with mRS score: fatal stroke (stroke with subsequent death), severe stroke (stroke followed by mRS of 4-5), moderate stroke (stroke followed by mRS of 2-3), mild stroke (stroke followed by mRS of 0-1), TIA, and no stroke/TIA)
 
• Myocardial infarction
 
                                                                                                                                                                                                                                                                                                                                                                                                                                                                                                                                                                                                                                                           |

|                             |                                                                                                                                                                                                                                                                                                                                                                                                                                                                                                                                                                                                                                                                                                                                                                                                                                                                                                                                                                                                                                                                                                                                                                                                                                                                                                                                                                                                                                                                                                                                                                                                                                   |
|-----------------------------|-----------------------------------------------------------------------------------------------------------------------------------------------------------------------------------------------------------------------------------------------------------------------------------------------------------------------------------------------------------------------------------------------------------------------------------------------------------------------------------------------------------------------------------------------------------------------------------------------------------------------------------------------------------------------------------------------------------------------------------------------------------------------------------------------------------------------------------------------------------------------------------------------------------------------------------------------------------------------------------------------------------------------------------------------------------------------------------------------------------------------------------------------------------------------------------------------------------------------------------------------------------------------------------------------------------------------------------------------------------------------------------------------------------------------------------------------------------------------------------------------------------------------------------------------------------------------------------------------------------------------------------|
|                             | 
 
• Vascular death
 
• All-cause death
 
• Poor functional outcome (mRS score 2-6)
 
• Poor quality of life (EuroQoL-5 Dimensions index score <math>\leq 0.5</math>)
 
• Early neurological deficits (increase in NIHSS score at 7days)
 
 
Primary safety outcomes:
Moderate to severe bleeding (Appendix 6)
 
Secondary safety outcomes:
 
 
• Intracranial hemorrhage
 
• Hepatotoxicity: alanine transaminase or aspartate transaminase > 3 times the upper limit of normal value after statin treatment.
 
• Muscle toxicity: creatine kinase > 10 times the upper limit of normal value, or the presence of muscle pain, myopathy or rhabdomyolysis.
 
• Death
 
• Other AEs/SAEs
 
                                                                                                                                                                                                                                                                                                                                                                                                                                                                                                                                                                                                                                                                                                                                                     |
| Statistical analysis | 
Statistical analysis will be conducted with SAS 9.4. The two-sided <math>P < 0.05</math> is considered statistically significant.
 
1. Major null hypothesis:
 
1) In patients with acute mild ischemic stroke or high-risk TIA patients attributed to extracranial or intracranial atherosclerosis treated within 72 hours of ictus, there is no difference in the risk of a new stroke within 90 days between subjects with intensive antiplatelet therapy and those with standard antiplatelet therapy.
 
2) In patients with acute mild ischemic stroke or high-risk TIA patients attributed to extracranial or intracranial atherosclerosis treated within 72 hours of ictus, there is no difference in the risk of a new stroke within 90 days between subjects with immediate intensive statin therapy (atorvastatin 80mg/d) and delayed intensive statin therapy (atorvastatin 40mg/d).
 
3) In patients with acute mild ischemic stroke or high-risk TIA patients attributed to extracranial or intracranial atherosclerosis treated within 72 hours of ictus, there is no difference in the risk of a new stroke within 90 days between subjects with intensive antiplatelet combined with immediate intensive statin therapy (atorvastatin 80mg/d) and standard antiplatelet combined with delayed intensive statin therapy (atorvastatin 40mg/d).
 
2. Data sets of statistical analysis : intention-to-treat (ITT) population
 
3. Statistical analysis methods:
 
3.1 The balance analysis of basic values (comparison between groups of baseline
 |

characteristics)

- 1) The measurement data will be tested by t test or Wilcoxon rank sum test;
- 2) The enumeration data between groups are compared with chi-square test, Fisher's exact probability method or Wilcoxon rank sum test.

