| Study Outcomes | 
Primary outcome:
 
Stroke (ischemic or hemorrhagic)
 
Secondary outcomes:
 
 
• Composite vascular events: stroke (ischemic or hemorrhagic), myocardial infarction, or cardiovascular death.
 
• Ischemic stroke
 
• TIA
 
• Severity of stroke or TIA on an ordinal scale (a six-level ordered category scale combined vascular events with mRS score: fatal stroke (stroke with subsequent death), severe stroke (stroke followed by mRS of 4-5), moderate stroke (stroke followed by mRS of 2-3), mild stroke (stroke followed by mRS of 0-1), TIA, and no stroke/TIA)
 
• Myocardial infarction
 
• Vascular death
 
• All-cause death
 
• Poor functional outcome (mRS score 2-6)
 
• Poor quality of life (EuroQoL-5 Dimensions index score≤0.5)
 
• Early neurological deficits (increase in NIHSS score at 7days)
 
 
Primary safety outcome:
 
Moderate to severe bleeding (Appendix 6)
 
Secondary safety outcomes:
 
 
• Intracranial hemorrhage
 
• Hepatotoxicity: alanine transaminase or aspartate transaminase > 3 times the upper limit of normal value after statin treatment.
 
• Muscle toxicity: creatine kinase > 10 times the upper limit of normal value, or the presence of muscle pain, myopathy or rhabdomyolysis.
 
• Death
 
• Other AEs/SAEs
 
 |

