### 4.2 Secondary outcomes:

- Combined vascular events : Stroke (ischemic or hemorrhagic), myocardial infarction, or cardiovascular death
- Ischemic stroke
- TIA
- Severity of stroke or TIA on an ordinal scale: (a six-level ordered category scale combined vascular events with mRS score: fatal stroke (stroke with subsequent death), severe stroke (stroke followed by mRS of 4-5), moderate stroke (stroke followed by mRS of 2-3), mild stroke (stroke followed by mRS of 0-1), TIA, and no stroke/TIA)
- Myocardial infarction
- Vascular death
- All-cause death
- Poor functional outcome (mRS score 2-6)
- Poor quality of life (EQ-5D scale index score  $\leq 0.5$ )
- Early neurological deficits (increase in NIHSS score at 7 days)

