### 16.3.1 Statistical analysis of data sets

**Full Analysis Set (FAS):** The full analysis set is the main efficacy evaluation population of this study, and all valid variables will be analyzed by FAS. According to the basic principle of intention-to-treat (ITT) analysis, all subjects randomized into groups and those with more than one medication record and efficacy evaluation will be included in the full analysis set. When choosing FAS to analyze, the estimate of the missing value, the last observation carried forward (LOCF) estimation method can be used.

**Per Protocol Set (PPS):** Includes all subjects who complete the protocol or have no serious breaches of the trial. The exact definition of a serious violation of the program will be finalized at the time of data review and may generally include the following situations (but not limited to these cases): failing to meet the main inclusion criteria, serious disturbance of drug efficacy after treatment, poor compliance, exceeding the time window of following-up and so on. PPS is the secondary analysis of the effectiveness of the crowd, but if the results are inconsistent with the whole analysis set, detailed analysis of the

inconsistent results are needed.

**Safety Data Set (SS):** A safety data set is defined as a subject that receives drug treatment at least once. In the entire safety analysis, patients with incorrect treatment (for example, randomized to the standard antiplatelet combining delayed intensive statin therapy groups were given enhanced antiplatelet therapy) would be assigned to the actual treatment group.

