**5- Severe disability; Requires constant nursing care and attention, bedridden, incontinent.**

Although no trained nurses are necessary, they need to be taken care of throughout the day and night.

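### Two secondary outcomes, poor quality of life (EQ-5D) and early neurological deficits (Day 7 NIHSS), give no place to patients who die before the assessment, and the permitted carry-forward would usually count them as good results

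*Supplement*

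**What the plan says.** All references are to protocol V4.0.

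- **Definitions.** The Summary lists "Poor quality of life (EuroQoL-5 Dimensions index score" of 0.5 or less), and section 4.2 repeats it as "Poor quality of life (EQ-5D scale index score" with the same cut-off. Section 2.2.1 places it at 90 days. Section 4.2 also lists "Early neurological deficits (increase in NIHSS score at 7 days"). Neither definition mentions death.
- **Comparator.** The same list has "Poor functional outcome (mRS score 2-6"). Appendix 2 ends at "5- Severe disability; Requires constant nursing care and attention, bedridden, incontinent", so the only state left for grade 6 is death. The six-level stroke severity scale on that list also has a fatal category.
- **Timing.** EQ-5D and NIHSS are taken on the day of randomisation (10.2). EQ-5D is next taken at Day 90 (10.5) and month 12 (10.6). The first scheduled NIHSS after baseline is at Day 7 (10.3). An NIHSS is also obtained when new or worsening neurological symptoms are suspected (10.7).
- **Missing values.** For the full analysis set, 16.3.1 says that "the last observation carried forward (LOCF) estimation method can be used". No other rule is given.
- **Analysis.** Section 16.3.2.2 assigns logistic regression to the mRS and NIHSS outcomes. It names no method for the EQ-5D outcome.
- **Scoring appendices.** Appendix 3 covers uncooperative and comatose patients, and Appendix 5 lets a family member complete the EQ-5D. Neither gives a value for a patient who has died.

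**The concern.** Both outcomes are dichotomies built on a reading that only a living patient can provide. Death is the worst result a patient can have, yet the text gives it no category. A dead patient has no unobserved quality of life or NIHSS to recover, so this is first a question of outcome definition. A general missing-data method does not settle it.

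At stake is the direction of the two comparisons. If one arm has fewer deaths and the patients saved survive with poor quality of life, that arm looks worse on the EQ-5D outcome. If one arm has more deaths, the excess does not show there. Either way the EQ-5D line can disagree with the mRS line in the same patients. A mortality difference is not far-fetched here, since intensive antiplatelet therapy could plausibly alter both fatal stroke and fatal bleeding.

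**Working it through.** There is no stated figure to reproduce, because the protocol gives no rate or power for these outcomes. The check has two parts.

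**1. What the rules do to a patient who dies**

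| Case | No carry-forward | Carry-forward as 16.3.1 allows |
|---|---|---|
| Death before Day 90, baseline EQ-5D above 0.5 | dropped | not poor |
| Death before Day 90, baseline EQ-5D 0.5 or less | dropped | poor |
| Death before Day 7, baseline is the last NIHSS | dropped | change 0, no deficit |
| Death before Day 7, raised event-triggered NIHSS (10.7) | dropped, unless that reading is used | deficit |
| Any death by Day 90, mRS outcome | counted as poor (grade 6) | counted as poor if grade 6 is assigned |

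Counting the death as good is therefore the usual result for EQ-5D under carry-forward, but not the only one.

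**2. How large the effect could be**

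Every rate below is an assumption. Let d be the proportion dead by Day 90 and q the proportion of survivors with an index of 0.5 or less.

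*Share of all dead-or-poor patients who are not counted* = d / (d + (1 − d)q):

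- d = 1%, q = 6%: 0.010 / (0.010 + 0.0594) = 14.4%
- d = 0.5%, q = 10%: 0.005 / (0.005 + 0.0995) = 4.8%
- d = 2%, q = 4%: 0.020 / (0.020 + 0.0392) = 33.8%

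*Example A, deaths replaced by poor survival.* Control: 1.5% dead, 6.0% alive with poor quality of life. Treated: 1.0% dead, 6.5% alive with poor quality of life.

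- Survivors only: 6.0/98.5 = 6.09% versus 6.5/99.0 = 6.57%. OR = (6.5/92.5) / (6.0/92.5) = 1.083, against treatment.
- Deaths counted as not poor: 6.0% versus 6.5%. OR = (6.5/93.5) / (6.0/94.0) = 1.09.
- Deaths counted as poor: 7.5% versus 7.5%. OR = 1.00.

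*Example B, excess deaths with equal survivor rates.* Mortality 0.5% versus 1.0%, which is about 15 versus 31 deaths at 3050 per factorial arm (6100/2).

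- Deaths excluded: OR 1.00.
- Deaths counted as not poor: OR about 0.995.
- Deaths counted as poor: OR 1.145 (q = 3%), 1.092 (q = 5%), 1.048 (q = 10%). For q = 5%: 0.05 × 0.995 + 0.005 = 5.475% versus 0.05 × 0.99 + 0.01 = 5.95%.

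*Equal mortality and equal survivor rates.* OR 1.00 under all three codings. Only the level moves. With q = 5% and d from 0.5% to 2%, the proportion is 5.0% with deaths excluded, 4.9% to 5.0% with deaths counted as good, and 5.5% to 6.9% with deaths counted as poor.

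*Day 7.* An assumed mortality of 0.1% to 0.5% is 3 to 15 deaths per factorial arm, so the NIHSS outcome has little room to move.

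**The case against.** The strongest reply is that 16.3 calls itself an overview and defers to a final SAP that is not in the supplement. Coding rules for score-based outcomes commonly sit there, and Appendix 5 does not even give the algorithm for the index. That disposes of any complaint about silence alone. It does not dispose of this point. The outcome definition is protocol content, the list already makes room for death in two other outcomes, and the one missing-value rule that the protocol states points the wrong way when applied across death. If the SAP already classifies death, only alignment is needed.

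Second, a reader might infer that a patient who dies can never meet either outcome. The documents do not support that. Carry-forward is optional, a baseline EQ-5D of 0.5 or less would carry forward as poor, an event-triggered NIHSS may record a rise before death, and nothing forbids a worst-value rule.

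Third, a reader might infer that fatal harm could go unnoticed in the trial. It could not. All-cause death, vascular death, fatal stroke on the ordinal scale and mRS 2-6 are efficacy outcomes, death is again a safety outcome, and fatal bleeding is graded severe within the primary safety outcome.

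Fourth, the sizes are assumed, and Example A is built so that deaths and poor survivors offset exactly. With about 183 versus 198 events, its OR of 1.083 has a standard error of about 0.106 on the log scale, so z is about 0.75. It would not produce a false significant result. That is fair, but an unstable direction still matters for an outcome that will be read beside mRS.

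Finally, reporting quality of life in survivors with mortality beside it is a legitimate alternative. It has to be stated, though, and it is no longer a comparison of the groups as randomised.

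**Conclusion.** The point holds in a limited form. V4.0 gives patients who die before the assessment no category in the EQ-5D and Day 7 NIHSS outcomes, unlike mRS 2-6. They either drop out or, under the carry-forward that the protocol permits, are usually counted as not poor, or as no deficit when baseline is the last NIHSS.

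This can bias the comparison between arms if mortality differs. The amount cannot be derived from the documents. Under the assumed rates it is a shift in the odds ratio of roughly 5% to 15%, and equal mortality cannot by itself create a difference. The Day 7 effect is probably small, since patients enter with TIA or NIHSS of 5 or less; few early deaths is itself an assumption. The damage is confined to these two secondary outcomes. The primary outcome, its power and the mortality and safety reporting are untouched. It should be corrected because the correction is simple, not because the main conclusions are at risk.

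**What to change.** In the Summary, section 4.2 and the SAP:

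1. Define poor quality of life as an EQ-5D index of 0.5 or less, or death, by Day 90.
2. Define the early neurological outcome as a rise in NIHSS, or death, by Day 7.
3. State the exact cut-off day for counting a death, given the visit windows of ±7 and ±2 days.
4. Report the death component and the survivor component on separate lines for each outcome.
5. In 16.3.1, state that no value is carried forward past death.
6. In 16.3.2.2, name logistic regression for the EQ-5D outcome.

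The cost is a few lines of text, and deaths are already collected, so no new data are needed. The downside is small: both outcomes become composites with death, so the second no longer measures neurological change alone. The separate component lines are there to keep that visible.
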